### 9.2.2 SAEs related to investigational drug

Such SAEs are defined as SAEs that appear to have a reasonable possibility of causal relationship.

### 9.2.3 Suspected unexpected serious adverse reactions (SUSARs)

SUSARs are all serious adverse reactions with **suspected** causal relationship to the study drug that is **unexpected** (not previously described in the Summary of Product Characteristics or Investigator's brochure) and serious.

### 9.2.4 Pregnancy

Any pregnancy that occurs during study participation must be reported to the Investigator/sponsor. To ensure subject safety, each pregnancy must be reported to the Sponsor immediately. The pregnancy must be followed up to determine outcome (including premature termination) and status of mother and child. Pregnancy complications and elective terminations for medical reasons must be reported as an AE or SAE. Spontaneous abortions must be reported as an SAE.

Any SAE occurring in association with a pregnancy brought to the Investigator's attention after the subject has completed the study and considered by the Investigator as possibly related to the investigational product, must be promptly reported to the Investigator/sponsor.

In addition, the Investigator must attempt to collect pregnancy information on any female partners of male study subjects who become pregnant while the subject is enrolled in the study. Pregnancy information must be reported to the Investigator/sponsor as described above.

## 9.3 Severity of adverse events

The severity of clinical AEs is graded on a four-point scale: mild, moderate, severe, life-threatening and reported on specific AE pages of the CRF.

If the severity of an AE worsens during study drug administration, only the worst intensity should be reported on the AE page. If the AE lessens in intensity, no change in the severity is required.

### **Mild**

Event may be noticeable to subject; does not influence daily activities; the AE resolves spontaneously or may require minimal therapeutic intervention;

### **Moderate**

Event may make subject uncomfortable; performance of daily activities may be influenced; intervention may be needed; the AE produces no sequelae.

### **Severe**

Event may cause noticeable discomfort; usually interferes with daily activities; subject may not be able to continue in the study; the AE produces sequelae, which require prolonged therapeutic intervention.

A mild, moderate, severe AE may or may not be serious. These terms are used to describe the intensity of a specific event (as in mild, moderate, or severe myocardial infarction). However, a severe event may be of relatively minor medical significance (such as severe headache) and is not necessarily serious. For example, nausea lasting several hours may be rated as severe, but may not be clinically serious. Fever of 39°C that is not considered severe may become serious if it prolongs hospital discharge by a day. Seriousness rather than severity serves as a guide for defining regulatory reporting obligations.

## 9.4 Relationship to study drug

For all AEs, the Investigator will assess the causal relationship between the study drug and the AE using his/her clinical expertise and judgment according to the following algorithm that best fits the circumstances of the AE:

### **Not related**

- May or may not follow a temporal sequence from administration of the study product
- Is biologically implausible and does not follow known response pattern to the suspect study drug (if response pattern is previously known).
- Can be explained by the known characteristics of the subject's clinical state or other modes of therapy administered to the subject.

### **Unlikely**

- There is a reasonable temporal relation between the AE and the intake of the study medication, but there is a plausible other explanation for the occurrence of the AE.

### **Possibly**

- The AE has a reasonable temporal relationship with drug administration.
- The AE may equally be explained by the study subject's clinically state, environmental or toxic factors, or concomitant therapy administered to the study subject.

- The relationship between study drug and AE may also be pharmacologically or clinically plausible.

**Probably**

- There is a reasonable temporal relation between the AE and the intake of the study medication, and plausible reasons point to a causal relation with the study medication.

**Related**

- Reasonable temporal relation between the AE and the intake of the study medication and
- There is no other explanation for the AE and
- Subsidence or disappearance of the AE on withdrawal of the study medication and
- Recurrence of the symptoms on restart at previous dose (only applies for re-institution of medication).

**Not assessable**

- The causal relationship between the study drug and the AE cannot be judged.

## 9.5 Reporting procedures

A special section is designated to adverse events in the case report form. The following details must thereby be entered:

- Type of adverse event
- Start (date and time)
- End (date and time)
- Severity (mild, moderate, severe, life-threatening)
- Serious (no / yes)
- Unexpected (no / yes)
- Outcome (resolved, resolving, not resolved, resolved with sequelae, unknown, fatal)
- Relation to study drug (Related/ Probably/ Possibly/ Unlikely/ Not related/ Not assessable)

Adverse events are to be documented in the case report form in accordance with the above-mentioned criteria.

### 9.5.1 Reporting procedures for SAEs

In case of a serious adverse event, the Investigator has to use all supportive measures for best patient treatment. A written report is also to be prepared and should at least contain the following:

- Patient number
- Patient: sex
- The suspected investigational medical product (IMP)
- The adverse event assessed as serious
- Short description of the event and outcome

If applicable, the initial report should be followed by the Follow up report, indicating the outcome of the SAE.

### 9.5.2 Reporting procedures for SUSAR

It must be remembered that the regulatory authorities, and the Institutional Review Board / Independent Ethics Committee (IRB / IEC) must be informed about all SUSAR. Such reports shall be made by the sponsor and should content at least the following details:

- Patient number (study code/screening number)
- Patient: age in years, sex
- Name of Investigator and investigating site
- Period of administration
- The suspected investigational medical product (IMP)
- The adverse event assessed as serious and unexpected, and for which there is a **suspected** causal relationship to the IMP
- Concomitant disease and medication
- Short description of the event:
  - Description
  - Onset and if applicable, end
  - Therapeutic intervention
  - Causal relationship
  - Seriousness criteria or reportable reason

Electronic reporting should be the expected method for reporting of SUSARs to the competent authority within 7 calendar days for fatal/life-threatening events and within 15 calendar days for all other serious events. In that case, the format and content as defined by the regulatory requirements should be adhered to. The latest version of MedDRA should be applied. Lower level terms (LLT) should be used.

### 9.5.3 Development safety update report

A Development Safety Update Report (DSUR) will be provided by the Sponsor annually.

This report will also be presented annually to the Independent Ethics (IEC) and to the competent authorities by the sponsor.

## 10 FOLLOW-UP

### 10.1 Follow-up of study participants including follow-up of adverse events

The study will end for the individual patient on day 29. However, in case of ongoing SARS-CoV-2 disease or ongoing side effects regular check-ups (e.g. once a week) will be performed to follow-up on the outcome. Importantly, given the special circumstances these follow-ups will be performed by telephone calls, if possible.

### 10.2 Treatment after end of study

Within the scope of the study treatment for patients is planned for 1-7 days (28 days for asunercept, 5 days for pentaglobin, 5-10 days for remdesivir). The optimal duration of treatment is currently unknown. Further treatment of patients will be decided by treating physicians on an individual basis. In case of improvement of patient status, a prolonged treatment is not required for patients. In case of a deterioration of the patient status, discharge from hospital may not be possible and patients may receive other treatments.

## 11 STATISTICAL METHODOLOGY AND ANALYSIS

The statistical analysis in the protocol are outlined for the main part A. More details will be provided in statistical analysis plan (SAP), which will be finalized before the first interim analysis. For sub study A, B and C separate statistical analysis plans (SAPs) will be developed. Importantly, each part of the study (e.g. Asunercept, pentaglobin, etc.) will have its own control group (randomized vs. standard of care) and will therefore be judged as an independent trial within the platform trial. Thus, the first patient in the asunercept trial is the first patient randomized to asunercept vs. standard of care and not the first patient in the platform trial. **This is necessary because background therapy is constantly changing in COVID-19 treatment such as by the introduction of remdesivir or dexamethasone.**

### 11.1 Analysis sets

#### Two different analysis sets are defined

##### (Modified) Intention to treat set

This analysis set includes subjects who were randomized (and received at least one dose study drug).

##### Per-protocol set

This analysis set comprises all subjects who received study drug (at least one dose) and did not violate the protocol in a way that might affect the evaluation of the effect of the study drug(s) on the primary objective, i.e., without major protocol violations.

### 11.2 Sample size considerations

There is currently only limited or no data available on expectable effect sizes. A preliminary sample size calculation was performed based on the primary endpoint defined as time-to-clinical improvement for the comparisons of two groups.

Based on the recent publication of Cao et al. (1) we assumed that the median time in the treatment arm 2 (Lopinavir/Ritonavir) is about 16 days. Assuming an improvement between two groups of 6 days in the median time to clinical improvement, a **log-rank test at a two-sided significance level of  $\alpha = 0.05$**  with a sample size of 100 per treatment group would yield a power larger >80%. These assumptions would translate in a hazard ratio of 1.6 when assuming exponential time-to-event curves.

The sample size calculation was performed with N-Query: When the sample size in each group is 100, with a Total number of events required, E, of 154, an exponential maximum likelihood test of equality of survival curves with a 0,05 two-sided significance level will have 83,15% power to detect the difference between a Group 1 exponential parameter,  $\lambda_1$ , of 0,069 and a Group 2 exponential parameter,  $\lambda_2$ , of 0,043, (a constant hazard ratio of 1,6).

Two interim analyses are planned. The first interim analysis is planned after 20 patients have been included in the open study arms in at least 2 groups. A second interim analysis is planned after 50 patients in a treatment arm and this can trigger a sample size re-calculation.

Possibly, treatment arms may also be closed at the interim analyses.

## 11.3 Relevant protocol deviations

All protocol deviations will be listed in the study report.

## 11.4 Statistical analysis plan

Patient demographics and baseline characteristics will be summarized on the ITT set, overall and by treatment cohort, by means of summary descriptive statistics.

For qualitative variables (e.g. sex), absolute (n= ) and relative frequencies will be calculated per treatment group. Data will be visualized by bar plots. For quantitative data (e.g. age), the number of valid observations (n = ), mean, standard deviation, standard error, median, minimum and maximum will be calculated for each treatment group and each time point separately. Data will be visualized by boxplots and histograms.

## 11.5 Missing, unused and spurious data

Missing data will not be imputed.

## 11.6 Endpoints analysis

### 11.6.1 Primary endpoint analysis

All primary analyses will be on the modified ITT set and the analysis based on the per protocol set will be provided as supportive analysis.

The primary endpoint is time to clinical improvement which is defined as time from randomization to an (sustained) improvement of at least one category on two consecutive days compared to the status at randomization measured on a seven-category ordinal scale (proposed by WHO).

The 7-categories of the World Health Organization proposed scale, as follows:

1. Not hospitalized, no limitations on activities
2. Not hospitalized, limitation on activities;
3. Hospitalized, not requiring supplemental oxygen;
4. Hospitalized, requiring supplemental oxygen;
5. Hospitalized, on non-invasive ventilation or high flow oxygen devices;
6. Hospitalized, on invasive mechanical ventilation or ECMO;
7. Death.

During hospitalization this score will be determined daily (till day 29). If a patient is released from the hospital before day 29, the score will be determined at day 11 and 29 (and day 60 in clazakizumab arm) after randomization (depending when the patient was released or by telephone call).

The time to clinical improvement will be visualized by Kaplan-Meier Plots. The comparisons of the time-to-event curves will be performed using a log-rank at a two-sided level alpha of 5%.

(Please note in the initial phase only treatment arms (1-3, 5) might be available for the platform trial. A closed test procedure will be implemented to control the multiple level alpha. More details will be provided in the statistical analysis plan.

Additionally, a Cox-proportional hazard model will be performed. In this model we will use treatment as factor and it will be adjusted for calendar time to account for time trends (e.g. severity of cases might change over time).

Furthermore, we will include sex and age as factors in the model.

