### 6.1 Primary objective

To investigate the efficacy of various experimental therapeutics for patients with laboratory-proven SARS-CoV-2 infection. A 7-category ordinal scale for clinical severity assessment as proposed by the World Health Organization will be used for efficacy assessment:

- Time to sustained (>48h) improvement of one category from admission
- Clinical status, assessed once daily
- Mean change in the ranking on an ordinal scale from baseline (assessed once daily)

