### 8.5.3 Treatment phase (First Day of Treatment = Day 1)

For treatment arms 2 the minimum duration of treatment is seven days but at least until sustained improvement. For treatment arm 3 (remdesivir) treatment duration is 5-10 days. In case of an early discharge from hospital (before 7 days) patients will receive the required treatment to take it at home (treatment arms 2). In case of an early discharge patients will be called (by telephone) on day 11 and 29 to obtain information on the clinical endpoints.

For all patients the clinical endpoints (including WHO ordinal scale, NEW Score, oxygenation, etc.) will be obtained on a daily basis.

Blood pressure, heart rate, respiratory rate, oxygen demand, oxygen saturation, mode of oxygen delivery, concomitant medication is documented as part of routine care. Laboratory analyses (similar to screening investigation, without HBsAg, but with D-Dimer and anti-FXa activity and troponin levels only between day 5 and 11) will be performed three times a week, and in case of clinical necessity possibly more often.

Blood sampling is recommended three times a week, if possible (e.g. Mo, Wed, Fr), to monitor patients for medical reasons. If this is not feasible because it is against hospital rules or puts too much burden on the already stressed health care workers, the frequency of blood sampling can be reduced without being a protocol deviation.

If such assays are available, pharmacokinetic measurements of antiviral substances will be performed (e.g. trough level analysis for lopinavir/ritonavir after 24h and on day 4 to 7).

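### The protocol does not say how discharge alive counts toward the sustained-improvement primary event, and its scoring schedules conflict: after release the scale is scored only on days 11 and 29

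*Protocol*

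**What the plan says.** **The event.** Section 11.6.1 defines the primary event as "improvement of at least one category on two consecutive days compared to the status at randomization". Section 6.1 states it as "Time to sustained (>48h) improvement of one category from admission", and the statistical row of the synopsis also uses more than 48 hours. The efficacy-endpoint row of the synopsis carries both versions.

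**The scoring schedule.** Section 11.6.1 has the scale scored daily during the hospital stay, and then "If a patient is released from the hospital before day 29, the score will be determined at day 11 and 29". Section 8.5.3 agrees: "In case of an early discharge patients will be called (by telephone) on day 11 and 29". For asunercept, the adjunctive-therapy part of Section 8.5.3 ends daily collection at discharge or death.

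**The contrary statements.** Directly after the sentence on telephone calls, Section 8.5.3 says: "For all patients the clinical endpoints (including WHO ordinal scale, NEW Score, oxygenation, etc.) will be obtained on a daily basis". The statistical row of the synopsis has the scale measured every day to day 29. Table 1 marks it in the column for all treatment arms, which spans days 1 to 29.

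**Missing scores.** Section 11.5: "Missing data will not be imputed".

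**Discharge.** On the seven-category scale, a patient out of hospital is in category 1 or 2, better than any in-hospital category. No section says whether that status counts toward the confirmation period, or on what date.

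**The concern.** Confirming an improvement takes scores on adjacent days, and after release the schedule in 11.6.1 supplies two isolated ones. Main-study patients need oxygen support at entry (Section 7.1.2), so they start in category 4 or worse. A category-4 patient who goes home straight from oxygen, or soon after coming off it, may leave with at most one improved score. Taken at face value, the schedule and the no-imputation rule then give that patient either no event or an event dated at a later call, although the patient has plainly improved.

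The primary comparison is at stake. Lost events cost power. The analyst must also decide whether such a patient is censored at discharge or stays in the risk set to day 29, and the two choices give quite different results. In an open-label trial, discharge practice could also differ between arms for reasons other than recovery.

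**Working it through.** **1. Which patients are affected.** Take a patient in category 4 at randomization.

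- Two improved daily scores in hospital: the event is met under the two-day rule, whatever happens later. More than 48 hours may still be incomplete at release.
- One day in category 3, then home: two improved days if the discharge day is scored, one if it is not. The protocol does not say.
- Home directly from category 4: at most one improved score, on the day of discharge. The next scores are isolated.
- Home on day 10 or day 28: a discharge-day score can pair with the call on day 11 or 29.
- Home on day 12: next scored on day 29, which is 29 − 12 = 17 days later.

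**2. The plan's own power.** Inputs from Section 11.2: 100 per group, 154 events, hazard ratio 1.6 (rates 0.069 and 0.043 per day), two-sided alpha 0.05, stated power 83.15%.

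Schoenfeld: power = Φ(√E × ln(HR)/2 − 1.960) = Φ(√154 × 0.470/2 − 1.960) = Φ(0.956) = 83.05%. The stated figure reproduces.

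Expected events at 28 days: 100 × (1 − e^(−0.069×28)) + 100 × (1 − e^(−0.043×28)) = 85.5 + 70.0 = 155.5, consistent with 154.

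**3. Margin.** Events for 80% power: 4 × (1.960 + 0.842)² / 0.470² = 142.1, so 143. The margin is 154 − 143 = 11 events, or 7%.

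**4. Equal loss in both arms.** Let q be the share of events lost. It is an assumption; the protocol gives no figure. If these patients are censored at discharge, the hazard ratio is unchanged and E becomes 154 × (1 − q). If they stay at risk without an event to day 29, the hazard ratio is diluted as well, so that case was simulated (log-rank, 1,500 runs, 100 per arm, medians 10 and 16 days, daily event times, lost improvers chosen at random).

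| q | Events, 154 × (1 − q) | Power, censored (formula) | Power, at risk to day 29 (simulated) | Estimated HR, at risk |
|---|---|---|---|---|
| 0 | 154 | 83.1% | 84% | 1.63 |
| 5% | 146.3 | 81.1% | not run | not run |
| 10% | 138.6 | 79.0% | 68% | 1.53 |
| 20% | 123.2 | 74.2% | 54% | 1.46 |
| 30% | 107.8 | 68.4% | 40% | 1.40 |

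Simulating the censored case gives 83%, 80%, 73% and 70% at q = 0, 10%, 20% and 30%, in line with the formula.

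**5. Unequal loss.** Illustration: 30% lost in the faster arm and 20% in the other, same simulation.

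| Truth | Censored at discharge | At risk to day 29 |
|---|---|---|
| HR 1.6 | power 42%, HR 1.41 | power 13%, HR 1.16 |
| No difference | rejects 11%, HR 0.87 | rejects 16%, HR 0.83 |

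With no true difference, the arm that loses more events looks worse and the test rejects more often than 5%. The direction follows the imbalance: if the slower arm lost more, a true effect would be exaggerated.

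**The case against.** A reader might infer that early-discharged patients can never register an event. The documents do not support that. Two improved inpatient scores already suffice under the two-day rule. Patients entering in category 5 or 6 would normally improve by a category while still in hospital. Discharge on day 10 or 28 can pair with a call. Anticipated discharge within 48 hours is an exclusion (Section 7.1.3), which shrinks the affected group, although it applies only at enrolment. The synopsis, Table 1 and one sentence of Section 8.5.3 also indicate daily scoring to day 29. All of this stands, so the fault is a conflict between stated rules and not an endpoint that is plainly unobtainable.

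It can also be said that status after discharge follows from the scale's own definition. Applying that definition is not imputation, and the calls are made "patients will be called (by telephone) on day 11 and 29 to obtain information on the clinical endpoints", which could include status since release. This stands too, and it is why the fix is cheap. The rule could be placed in the SAP, which is not shown. But the protocol itself fixes the event, the schedule and the ban on imputation, and as written they do not fit together.

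A reader might further infer that the better arm must lose more events, so that the bias always runs toward no difference. Nothing in the protocol establishes this, and the simulation removes improvers at random, so it does not model selective loss of the fastest recoveries.

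Nor does the ±7-day follow-up window in Table 1 disturb the primary score. The WHO-scale row has no mark in that column, and mortality is followed to days 60 and 90 (Section 8.5.4).

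**Conclusion.** The concern holds as a conflict on the primary endpoint. The event needs adjacent-day confirmation, the post-discharge schedule in 11.6.1 generally cannot supply it, other places say scoring is daily, and no rule states how discharge alive counts. Those affected are patients released before a second improved score, mainly those in category 4 at entry, with more affected if the criterion is more than 48 hours.

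The size is conditional. At an assumed 10% loss in both arms, power falls from about 83% to about 79% or about 68%, depending on whether lost patients are censored at discharge or kept at risk to day 29. The protocol specifies neither treatment and supports no particular loss share. Unequal loss could bias the comparison in either direction. These figures show why the rule must be written down; they do not forecast what the trial would lose. With discharge counted toward confirmation, no events are lost by this route and the planned 154 events and roughly 83% power stand.

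**What to change.** 1. Choose one confirmation criterion, two consecutive days or more than 48 hours, and use it in the synopsis and Sections 6.1 and 11.6.1.
2. Reconcile the scoring schedule across the synopsis, Table 1, both parts of Section 8.5.3 (including the asunercept text) and Section 11.6.1.
3. Add a rule to Section 11.6.1, for example: *A patient discharged alive is in category 1 or 2 from the day of discharge until readmission or death. This status counts toward the confirmation period. The event is dated at the first improved day. Readmission to a non-improved category, or death, within the confirmation period cancels it.*
4. Derive post-discharge status from the dates of discharge, readmission and death, checked at the existing day 11 and day 29 calls. Use the same derivation for the daily ordinal status in Section 11.6.2, and note in Section 11.5 that it is not imputation.

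The rule should end at readmission or death. Treating discharge as category 2 or better on every later day would misclassify patients who return to hospital or die.

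The cost is a short text amendment with no extra visits. The small downside is that status between discharge and the next call is derived and not scored.
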